##### Internal sensors of the smartphone

1.4.3.2

The smartphone's microphone is used for daily voice recordings. Participants are provided with daily varying stimulus material from a set of 16 questions (see Supplementary Material) to make voice recordings of 30 s within the iTD-App. For this purpose, up to four questions are offered as stimulus material. The questions are randomly selected daily to provide variety. Voice recordings are processed to extract phonetic parameters (e.g. frequency, pitch), but will NOT be analysed in terms of content (i.e., no natural language processing, NLP).

##### Data from the operating system

1.4.3.3

Data on the active use of the smartphone is routinely collected from the operating system of the smartphone itself. This data is collected through the iTD-App, limited to: app usage (e.g., social media, gaming apps, other apps; recorded in usage time and data volume), messaging behavior (time and data volume spend on messaging), and phone calls (duration and amount of incoming, outgoing and missed calls). In addition, called contacts are recorded anonymously. For this, the iTD-App assigns a hash code to each phone number and collects the information about which hash code has been contacted through calls. No personal data about the contacts (such as the phone numbers and names of the contacts) is recorded.

### Data management and privacy

1.5

The legal basis of the data processing is the voluntary consent (Art. 6 (1) (a) GDPR): Data is only collected and included if participants consent to data processing by written informed consent after having read the participant information and data processing information. Permissions are also requested within the iTD-App for the use of the individual sensors.

Upon first contact with the study centre, a Participant Identification Code (PIC) is assigned to each interested participant. All data collected during the study is stored pseudonymized using this PIC. A list with all study participants, i.e. their name, PIC and status (included/excluded, study ongoing/discontinued/completed) is kept confidentially at the study centre. The PIC is linked to an automatically generated UUID (Universally Unique Identifier) in the iTD app. This UUID serves as a pseudonymized identifier for the user, which is used throughout the backend architecture of the iTD-App, particularly on the MONDY platform. The UUID is automatically generated to ensure high security and global uniqueness while maintaining the anonymity of user data. All personal data are subject to confidentiality and can only be viewed by authorized persons.

Data collected from the iTD-App is stored in two databases, one for the pseudonymized demographic data and the other one for health data on the MONDY platform. The server systems are hosted in Germany. All data streams from the iTD-App are stored in a database, an IBM firestore©; the Fast Healthcare Interoperability Resources (FHIR®) spec 4.3.0 is used as the data schema. To access the database via a FHIR API (Application Programming Interface), authentication with a personal account (username and password) is required. Only project consortium members have access.

In a Machine Learning Operations (MLOps) system [48], the collected data is used to train statistical models. To do so, the raw measurement data from the FHIR system are synchronized with the Scientific Cluster infrastructure of Leipzig University. Therefore, deleted data (e.g., upon user request) will also be deleted on this system. The training of the statistical models is done in multiple consecutive steps (e.g., data cleaning, data pre-processing, missing data handling). All intermediate results (i.e., transformed data) are deleted immediately when the processing step has been finished. Finally, the trained model is stored in a database, including meta-information about which kind of data from which participant has been used to train this model. This ensures that models can be deleted if a participant requests their data to be deleted. We are examining for which scenarios differential privacy methods can be used sensibly to prevent information leakage from our models.

### Data analysis

1.6

The current study does not encompass confirmatory hypothesis testing and has explorative character, aiming to provide proof-of-concept for the value of personalized monitoring and forecasting of depression severity in individual patients. Missing data will be handled with model-specific imputation when needed.

To answer RQI, i.e. “Can personal MS data be an objective marker of the a) daily and b) weekly self-reported depressive symptom severity?“, we will conduct multilevel correlations between depressive symptom severity (PHQ-2, PHQ-9) and features derived from MS data through the application of data-driven methods. Multilevel approaches can be applied for statistical analyses of idiographic data [49,50]. Multilevel correlations will include participants as fixed effects and as random effect. All MS features will be included in the mixed model as fixed effects. However, in multilevel models, within-person variability is pooled across individuals, rather than person-specific [51]. Therefore, we will repeat analysis for each participant separately (truly idiographic *N* = 1 version of the analysis) to understand whether there are any differences in results if the data base is limited to MS features derived from personal data of the individual only. Apart from the correlations themselves, the effect sizes will be assessed to understand the clinical relevance of associations and a Random Forest classifier will be used to account for non-linear associations and to asses feature importance using Kernel SHAP analysis [52]. To validate our findings on an idiographic level, we will explore the use of unified structural equation modelling (USEM, [53,54]), including Group Iterative Multiple Model Estimation (GIMME; [55,56]) that can estimate both group-level relationships and individual-specific relationships.

To address RQII, i.e. “Can personal MS data predict the self-reported depressive symptom severity on a) the next day(s) and/or b) the next week(s)?“, we apply various machine learning techniques. Exploratory analyses investigate the predictability of depressive symptoms within individuals, using either classification or regression approaches. We compare idiographic models, which use data from individual patients, with nomothetic models based on data from all participants. Furthermore, we plan to examine whether multitask-learning methods [57] can enhance performance. Modern machine learning models, such as deep neural networks (DNNs), are validated against classical state-of-the-art methods, including boosted ensemble techniques [58], support vector machines [59], and autoregressive models [32] focusing on vector autoregressive (VAR) models and their analyses using forecast error variance decomposition (FEVD) and impulse response functions (IRF) specifically for idiographic approaches. Individual thresholds for high depressive symptom severity are derived from the data. Using eXplainable AI (XAI) methods, we evaluate the sensor technology component within iTD to understand the significance and impact of various MS features on the model's outcomes. This will help to identify the most relevant aspects of the MS data and clarify their influence on potential decision-making processes. Models based on data from all participants are validated using leave-one-subject-out cross-validation (LOSO-CV) [60,61], while within-subject models employ time-series cross-validation [62,63] and rolling back cross-validation [64].

For both RQ, sensitivity analyses will be conducted using different amounts of input data (e.g., 12 vs. 24 h of MS data, all AA vs. only MS data).

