### Design

1.1

This exploratory study uses an observational n-of-1 design [36], involving repeated measurements of self-reported, behavioural, and physiological outcomes over the time of one year (365 days) within individuals without manipulation of variables by the investigators. The work is carried out in accordance with the World Medical Association Declaration of Helsinki [37]. Ethical approval has been granted by the Ethics Committee of the Department of Medicine at Goethe University Frankfurt, Germany (date: 24/08/2023, reference number: 2023–1309). The study protocol has been registered in the German Clinical Trials Register (reference number: DRKS00032618).

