#### Trial status

1.3.3

Recruitment started in August 2023, first patient in was September 27, 2023, last patient out was December 02, 2024.

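### The main RQI mixed model and its single-patient repeats name no term for serial dependence, so run as described they would understate the uncertainty of within-person associations

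*Protocol article*

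**What the plan says.** The Design section sets repeated measurement "over the time of one year (365 days) within individuals". RQI uses an evening PHQ-2 and a weekly PHQ-9, so each person contributes up to 365 daily and about 52 weekly outcome values.

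For RQI, the Data analysis section states that "we will conduct multilevel correlations between depressive symptom severity (PHQ-2, PHQ-9) and features derived from MS data". It then lists the model terms: "Multilevel correlations will include participants as fixed effects and as random effect" and "All MS features will be included in the mixed model as fixed effects". Because a multilevel model pools within-person variability, it adds that "we will repeat analysis for each participant separately". Effect sizes are to be read for clinical relevance. A Random Forest is added for non-linear associations, and USEM including GIMME is to be explored as validation at the individual level.

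The vector-autoregressive models and the time-series cross-validation are described under RQII. The section also declares: "The current study does not encompass confirmatory hypothesis testing and has explorative character". It gives no alpha, interval method or autocorrelation.

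**The concern.** RQI asks about association within a person over time. Participant effects take out differences in average level between people. They leave untouched the dependence of today's mood, sleep, activity or phone use on yesterday's. When outcome and feature both persist from day to day, the series holds less information than its number of rows suggests. A correlation or mixed-model coefficient computed as if residuals were independent then gets too small a standard error.

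The single-patient repeats are the most exposed, since all their information comes from one serial record. The aim is proof of concept that MS data can act as an objective marker in individual patients. Intervals that are too narrow make chance co-movement look like such a marker.

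**Working it through.** **Inputs from the article.** Daily series up to n = 365; weekly series about n = 52 (one year); 15 participants included, 10–12 complete cases expected. The article states no alpha, power or error rate for RQI, so there is no figure of its own to reproduce.

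**Assumptions.** Lag-1 autocorrelation phi from 0.2 to 0.9, first-order autoregressive series, and a two-sided 5% test used only as a yardstick.

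**Formula.** For two unrelated AR(1) series, the variance of the sample correlation is inflated by F = (1 + phi_x·phi_y)/(1 − phi_x·phi_y). Effective n is n/F, intervals should be √F times wider, and the actual rejection rate is 2·[1 − Φ(1.96/√F)].

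Example, phi = 0.5 in both: F = 1.25/0.75 = 1.667; effective n = 365/1.667 = 219; 1.96/√1.667 = 1.518; rejection rate 12.9%.

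| phi (both series) | F | √F | effective n of 365 | rejection, formula | simulated, n = 365 | simulated, n = 52 |
|---|---|---|---|---|---|---|
| 0.2 | 1.083 | 1.04 | 337 | 6.0% | 5.8% | 5.8% |
| 0.3 | 1.198 | 1.09 | 305 | 7.3% | 7.1% | 7.2% |
| 0.5 | 1.667 | 1.29 | 219 | 12.9% | 12.4% | 12.4% |
| 0.7 | 2.922 | 1.71 | 125 | 25.2% | 25.4% | 23.1% |
| 0.9 | 9.526 | 3.09 | 38 | 52.5% | 52.2% | 46.2% |

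Simulated columns use 20,000 unrelated pairs per cell. F depends on the product of the two autocorrelations, so unequal values matter less: 0.3 with 0.6 gives F = 1.18/0.82 = 1.439 and about 10%.

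**Do participant effects help?** Participant-centred pooled correlations over 12 or 15 unrelated persons reject about 7% (phi 0.3), 12–14% (0.5) and 24–26% (0.7). Pooling does not remove the inflation.

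**Drift and season.** This is a separate mechanism and adds to the first. Unrelated linear trends carrying 10% of the variance of each series, with phi 0 to 0.5, give about 48% rejections at n = 365 and 11–20% at n = 52. Annual cycles of random phase carrying 10% give 27–33% and 8–18%. The shares are assumptions.

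**Does modelling time order repair it?** Adding lagged outcome, lagged feature, linear time and an annual sine–cosine pair brings the rate for unrelated AR(1) series to 5.0–5.9% (n = 365 and 52, phi 0.3 to 0.9). This tests a fuller model than the main fix below requires.

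**The case against.** The study is exploratory, disclaims confirmatory testing and sets no alpha, so no promised error rate is broken. The article is a condensed account, and residual covariance is the kind of detail a full analysis plan often carries. It nowhere says that days are treated as independent. USEM/GIMME, which estimates lagged paths per person, is named within RQI. At phi 0.2 to 0.3 the inflation is trivial (6–7%), and all figures above are for one feature at a time, whereas the article enters all features jointly.

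Much of this stands and limits the point. It does not dispose of it. The article does list the terms of the RQI model and assigns its autoregressive models to RQII. Exploring USEM/GIMME as validation does not correct the correlations and effect sizes that will be read for clinical relevance. Exploratory estimates still need honest intervals.

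A further objection concerns the remedy. Each person contributes one annual cycle, so trend and season terms cannot be told apart from one slow depressive episode. For a single episode of 90, 120 or 180 days placed at random in the year (assumed lengths), linear time plus an annual sine–cosine pair absorbs about 58%, 71% and 82% of the episode's variance. Where a feature truly tracked the episode, the correlation in that simulation fell from 0.43 to 0.24, 0.47 to 0.20 and 0.50 to 0.15. This objection holds: a detrended association should not replace the unadjusted one.

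A reader might also infer from "first patient in was September 27, 2023, last patient out was December 02, 2024" that everyone entered within 67 days (2 December 2024 less 365 days is 3 December 2023, 67 days after 27 September) and so shared one season. That holds only for those who completed 365 days; a later entrant could have left early, and dropout is foreseen. Nor does the BDI-II entry threshold of 14 or more establish a downward drift; the article itself expects that symptoms may worsen.

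**Conclusion.** The point holds for the main RQI mixed model and its single-patient repeats: as described, they contain nothing that accounts for serial dependence, and participant effects do not supply it. If run that way, intervals are too narrow by a factor √F: about 1.09 at phi 0.3, 1.29 at 0.5, 1.71 at 0.7 and 3.09 at 0.9. Shared drift or season would add to this.

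These sizes rest on assumed AR(1) autocorrelations and on single-feature correlations. The problem is material from phi of about 0.5 in both series and minor at 0.2 to 0.3.

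Two stronger readings are tempting and not supported. One is that false positives will exceed a rate the study reports; it reports none, so the harm is to stated uncertainty and to the objective-marker interpretation. The other is that RQI ignores autocorrelation altogether; USEM/GIMME is named there, though only tentatively.

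**What to change.** In the RQI mixed model and in every single-patient analysis, state and use one of: AR(1) or similar residuals within participant; a lagged outcome; or autocorrelation-robust errors (Newey–West or block bootstrap). Report the effective sample size with each association. For the weekly series of about 52 values the model-based options are safer, because Newey–West errors tend to remain too small in short, persistent series. A lagged outcome also changes what the coefficient means (association given the previous value), so the choice should be stated.

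Report associations adjusted for time trend, season and weekday as a sensitivity analysis beside the unadjusted estimate, and say that one year per person cannot separate season from a slow episode.

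No new data are needed. The cost is some extra code, a few sentences in the analysis section, and wider intervals, so fewer single-patient associations will look clear-cut.

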##### Weekly self-report

1.4.2.2

The Patient Health Questionnaire-9 (PHQ-9, [44]) is used to assess the weekly self-reported depressive symptom severity. To this end, the original wording of the introductory sentence was changed to “Over the *last week*, how often have you been bothered by any of the following problems?“. The PHQ-9 is a short self-report measure of depressive symptoms that is able to detect changes in depression over time [45] and has been recommended as a general measure of depression severity by the DSM-5 [39]. Each item is rated on a four-point Likert scale ranging from 0 to 3, total scores range from 0 to 27. Higher scores indicate more severe depressive symptoms.

The Situational Self-Awareness Scale (SSAS, [46]) is used to assess weekly fluctuations in public and private self-awareness occurring at the time of self-monitoring during this study. Data can be used to clarify the relation between self-awareness, continuous self-monitoring, and depressive symptoms. The SSAS is sensitive to changes in self-awareness within individuals over time and across situations [46]. A German version is used which was created by two native German speakers using the double-translation and reconciliation procedure [47].

Additionally, participants are asked weekly about life events (“Were there any special events this week that concern you?“), with the option to enter a free text note in the iTD-App.

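### RQI.b, single-patient analysis: all sensing features against at most 52 weekly PHQ-9 values, with no out-of-sample check stated, so in-sample fit is inflated by about p/51 for p features

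*Protocol article*

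**What the plan says.** Section 1.6 (Data analysis) answers RQI with multilevel correlations between PHQ-2 or PHQ-9 and "features derived from MS data through the application of data-driven methods". On what enters the model it is explicit: "All MS features will be included in the mixed model as fixed effects". Because a multilevel model pools within-person variability, "we will repeat analysis for each participant separately", in order to see whether results differ when only one person's data are used. On interpretation, "the effect sizes will be assessed to understand the clinical relevance of associations".

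The weekly outcome is the PHQ-9, which "is used to assess the weekly self-reported depressive symptom severity" (section 1.4.2.2). Measurements run "over the time of one year (365 days) within individuals" (section 1.1).

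Section 1.6 adds a Random Forest classifier with SHAP analysis for RQI and says that unified structural equation modelling and GIMME will be explored as idiographic validation. Leave-one-subject-out and time-series cross-validation appear only in the paragraph on RQII. Section 2.1 concedes a risk of overfitting, but for predictive models.

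**The concern.** The rule that every MS feature enters is harmless where rows are plentiful. In the weekly analysis of a single patient they are not: there is one row per week for one year, and the features may number a sizeable fraction of the rows. In-sample fit then rises through chance alone.

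What is at stake is the comparison that the single-patient repeat exists to make. The pooled weekly model has 10 to 15 times as many rows, so its chance fit is small, while each patient's own model has a large one. A reader comparing the two could take that gap, and the scatter of coefficients between patients, as evidence of personal markers when it is partly or wholly noise. Since effect sizes are to be interpreted clinically and no held-out check is stated for RQI, the plan describes nothing that would separate the two.

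**Working it through.** The article states no R2 and no feature count, so there is no figure of its own to reproduce.

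**Rows per patient.** 365/7 = 52.1, so n is at most 52 weekly PHQ-9 values.

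**Features, p (assumed, with a range).**
- Low case: the research questions name six domains (sleep/deep rest, physical activity, smartphone usage, heart rate, heart rate variability, speech). One feature each gives p = 6.
- Tally of the measures named in the research questions and section 1.4.3, one summary each:
  - watch: accelerometer, steps, light, heart rate = 4
  - sleep/deep rest and heart rate variability = 2
  - two phonetic parameters = 2
  - "app usage (e.g., social media, gaming apps, other apps; recorded in usage time and data volume", that is 3 classes × 2 measures = 6
  - messaging time and volume = 2
  - calls: 3 counts and 2 durations (a missed call has none) = 5
  - contacts called = 1
  - total 4 + 2 + 2 + 6 + 2 + 5 + 1 = 22
- The phonetic and app lists are only examples, and features are derived by data-driven methods, so the true p may be lower or higher than 22.

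**Formula.** For ordinary least squares with an intercept and p features unrelated to the outcome, R2 follows Beta(p/2, (n − p − 1)/2), with mean p/(n − 1).

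**Weekly, one patient, n = 52.**

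| p | expected R2, no association |
|---|---|
| 6 | 6/51 = 0.12 |
| 12 | 12/51 = 0.24 |
| 15 | 15/51 = 0.29 |
| 22 | 22/51 = 0.43 |
| 30 | 30/51 = 0.59 |

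At p = 22 the 5th to 95th percentiles are 0.28 to 0.59. A simulation of 2,000 runs gave a mean of 0.432. Residual degrees of freedom are 52 − 22 − 1 = 29.

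**Missed weeks, p = 22.** n = 47: 22/46 = 0.48. n = 42: 22/41 = 0.54. n = 36: 22/35 = 0.63.

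**Autocorrelation, p = 22, n = 52.** Outcome and features simulated as mutually independent AR(1) series gave a mean R2 of 0.47 (rho 0.3), 0.55 (rho 0.5) and 0.68 (rho 0.7). Adjusted R2 averages about 0 without autocorrelation, but 0.07, 0.21 and 0.43 in these three settings, so adjustment alone is not a safe correction.

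**Comparison models, p = 22.**
- Daily, one patient, n = 365: 22/364 = 0.06.
- Pooled weekly, within-person, N patients: 22/(52N − N) = 22/(51N), which is 0.043 for N = 10, 0.036 for N = 12 and 0.029 for N = 15.

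The problem is therefore confined to the weekly single-patient analysis.

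**If the correlations are pairwise instead.** The expected null r2 is 1/51 = 0.02 per feature. The largest of 22 averages about 0.10 in simulation.

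**The case against.** Four arguments on the other side have weight.

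- *The inputs are not in the text.* No feature count is given, and that the fit is unpenalised is inferred from silence. A condensed article may leave estimation detail to a fuller plan. This stands, and is why the result is given as p/51 over a range. What remains is a stated rule, that all features enter as fixed effects, whose ordinary meaning is an unshrunken fit.
- *Model R2 is not a named output.* The plan speaks of correlations and effect sizes, which could mean one feature at a time. The problem would then be mainly one of multiplicity, and much smaller. Even in a joint least-squares fit, individual coefficients are imprecise rather than biased. Both points stand. However, the text puts all features into one model, and imprecise coefficients read for clinical relevance without a held-out check can still mislead.
- *The study is exploratory and concedes overfitting.* Disclaiming hypothesis tests does not remove optimism from an in-sample effect size, and the caveat in section 2.1 concerns prediction and offers no remedy for RQI.
- *Idiographic validation is planned.* The structural equation and GIMME step is only to be explored, uses the same weeks and is not held-out evaluation.

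A reader might also infer that the vector autoregressive models of RQII fail in the same way. The text does not support this: it does not say that they use every feature or weekly data, and time-series cross-validation is already planned for within-subject models there.

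**Conclusion.** The concern holds in conditional form. If p features enter each patient's weekly model jointly by ordinary least squares, chance alone gives an expected in-sample R2 of p/51: 0.12 to 0.59 for 6 to 30 features, and 0.43 at the assumed tally of 22. Missed weeks and autocorrelation push it up. At the same p the daily single-patient and pooled weekly models stay at or below about 0.06, so weekly individual results would look stronger than the pooled ones, and different from them, without any real signal.

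It is tempting to conclude that every patient would appear to have a strong personal marker profile. The article does not support that. It would require raw model R2 to be reported and taken at face value, and 22 is a tally of recorded measures, not a stated minimum. Nor does the point reach beyond one part of RQI: the daily analyses and the pooled weekly analysis are little affected.

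**What to change.** For the weekly single-patient analyses of RQI.b only:

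- Use a penalised fit (ridge or elastic net) with the penalty tuned inside forward-chained training weeks, or a small feature set fixed in advance.
- Report the time-series cross-validated fit, a method already planned for RQII, alongside the in-sample associations.
- State how many features entered and how many weeks were used, so that p/(n − 1) can be set beside any R2.

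The cost is a change of analysis wording. No new data are needed, which matters because the trial status section reports the last patient out in December 2024. The downside is that penalised coefficients are shrunken and some patients may show no weekly signal.

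### Feature rankings from Kernel SHAP (RQI) and XAI (RQII) are not tied to held-out prediction, so a chance-level model still yields a ranking, one that tends to favour slow-moving sensor features

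*Protocol article*

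**What the plan says.** All of this is in section 1.6 (Data analysis) of the protocol article.

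**RQI.** The lead analysis is linear: "we will conduct multilevel correlations between depressive symptom severity (PHQ-2, PHQ-9) and features derived from MS data", repeated for each participant separately. In addition, "the effect sizes will be assessed to understand the clinical relevance of associations". The non-linear part is a separate step: "a Random Forest classifier will be used to account for non-linear associations and to asses feature importance using Kernel SHAP analysis". A further check is tentative: "To validate our findings on an idiographic level, we will explore the use of unified structural equation modelling". No held-out step is described for the Random Forest.

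**RQII.** XAI methods, not named, are applied "to understand the significance and impact of various MS features on the model's outcomes". The stated use is: "This will help to identify the most relevant aspects of the MS data and clarify their influence on potential decision-making processes". These models do have validation: "Models based on data from all participants are validated using leave-one-subject-out cross-validation (LOSO-CV"), with time-series and rolling-back cross-validation for the within-subject models. The text does not make the XAI reading depend on the result of that validation.

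The study is described as exploratory, without confirmatory testing. Section 2.1 lists overfitting of individual models as a limitation.

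**The concern.** Kernel SHAP explains a model, not the patient. Observed PHQ values affect it only through the training of the forest. Whether the forest predicts new days is not an input. A forest that has fitted only noise therefore still returns a complete ranking.

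Daily sensor and mood series are likely to be autocorrelated, and this makes the ranking under noise uneven. A slowly drifting feature lets the forest recognise stretches of the year, and mood on neighbouring days is similar. Slow features then look important without being related to depression.

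What is at stake is a stated product of the study: which sensor streams matter, for whom, and how they might inform decisions. Rankings that differ between patients by chance would look like personalised markers, and personalised markers are what the study sets out to show.

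**Working it through.** The article gives no numerical figure to reproduce here. The check is by simulation.

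**From the document:** 365 days per participant (section 1.1); a Random Forest classifier with Kernel SHAP (section 1.6).

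**Assumed:** number of features, autocorrelations, forest settings, a median split of the outcome, and later days held out. Shapley values were obtained by permutation sampling, which targets the same quantity as Kernel SHAP with a marginal background.

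**Quantities:**
- SHAP importance of feature j = mean over days of |φ_j|. This depends on the fitted model and the features only.
- Share of the top feature = its importance / sum over all features.
- Held-out permutation importance = held-out AUC − held-out AUC after permuting feature j. This uses outcomes on unseen days.

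**Simulation A.** All series share one lag-1 autocorrelation (0, 0.5 or 0.8); 10 or 20 features; 270 training and 95 held-out days; 60 trees; 12 data sets per setting. The true effect equals the noise SD, so r = 1/√(1+1) = 0.71 with the underlying score. It was run with 10 features and autocorrelation 0 or 0.5.

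| | No association | One true feature |
|---|---|---|
| Training AUC | 1.00 | 0.999 |
| Mean held-out AUC | 0.48–0.53 | 0.78–0.79 |
| Top feature's share, 10 features (equal share 10%) | 16–20% | 51–52% |
| Top feature's share, 20 features (equal share 5%) | 10–13% | not run |
| Top/bottom ratio (median) | 2.7–6.1 | 15–17 |
| Held-out AUC drop, top feature | −0.013 to +0.019 | 0.26–0.28 |

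Computing SHAP on the held-out rows changes little with no association: mean |SHAP| of the top feature is 0.036–0.071, against 0.036–0.074 on training rows. Outcomes still do not enter.

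**Simulation B.** 20 features, 10 with autocorrelation 0.9 and 10 with none; outcome autocorrelation 0.6. Four implementations with 8 to 20 data sets per setting; ranges are across those that reported the figure.

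| | No association | r = 0.2 | r = 0.5 |
|---|---|---|---|
| Top/median ratio | 2.3–3.1 | – | 6.7–7.7 |
| Top feature's share | 10–12% | 12–13% | 23–27% |
| True feature ranked first | – | 35% of runs | all runs, where reported |

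- With no association, held-out AUC was 0.49–0.51 and the top feature was slow-moving in 85–90% of runs. Since 10 of 20 features are slow, 10/20 = 50% would be expected if speed did not matter.
- At r = 0.2, the range of the top share over single runs was 9–18%, against 8–16% with no association. A wrong, slow-moving feature ranked first in 55% of runs.
- At r = 0.3, the top share averaged 14% and the true feature ranked first in 60% of runs.
- Held-out permutation importance averaged 0.002 with no association and 0.18 for the true feature at r = 0.5.
- With 52 weekly values and no association, the top/median ratio was about 4 and held-out AUC 0.49.

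**Why a reference is needed.** With no association, held-out AUC in simulation A had a standard deviation of 0.05 to 0.09 between data sets. A single patient can therefore be well above 0.5 by chance, so a comparison with 0.5 alone is not enough.

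**The case against.** The strongest case on the other side has four parts.

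*SHAP is not the only source of relevance.* This stands. Correlations, per-person repeats, effect sizes and, if used, USEM/GIMME all use the outcomes. A reader might infer that relevance is read from SHAP alone, and the document does not support that. But the forest is there to catch what correlations miss, so a null correlation cannot confirm or refute its ranking, and USEM/GIMME is only to be explored.

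*RQII is different.* This stands in part. The XAI method is not named, so it cannot be assumed to be SHAP, and the models are cross-validated, so a chance-level model would be visible. Nothing stated, however, prevents its ranking from being interpreted.

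*SHAP does separate signal from noise.* This stands for strong effects, as the r = 0.5 column shows. One might be tempted to compare the total mean |SHAP| (0.39 with no association, 0.41 at r = 0.5) and conclude that attribution is blind to signal. That total mainly reflects the spread of the forest's predictions and is the wrong statistic. Likewise, a top feature in 100% of null runs is true by definition and is no error rate.

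*This is an exploratory study in a condensed article, and details may be in a fuller plan.* A performance condition may exist elsewhere. The point rests on what the article does fix: a named importance measure that ignores held-out outcomes, and a stated step from model explanation to relevance. Admitting overfitting as a limitation is fair, but it is no safeguard.

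**Conclusion.** The point holds in a limited form. The RQI forest's SHAP ranking is not tied to any stated held-out performance, and the RQII reading of relevance is not conditional on the cross-validation that is planned. With autocorrelated daily data and no association, the ranking leans to slow-moving features (about 85–90% of runs against 50%). Modest effects around r = 0.2 cannot be told from none without a reference, while effects around r = 0.5 can.

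These sizes rest on the assumed autocorrelations, 20 features, a median split and small numbers of simulated data sets, so they are approximate. The document does not say that a marker will be declared for every patient. That is a risk left open by the plan. The correction is worth making and does not call the design into question.

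**What to change.** In section 1.6:

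1. Apply the forward time-series splits planned for the RQII within-subject models to the RQI Random Forest as well, and report its held-out performance.
2. Judge feature importance in RQI and RQII by held-out permutation importance on later time blocks of the same patient.
3. Compare performance and importance with the same quantities after circularly shifting the sensor series against the PHQ series. This keeps the autocorrelation and breaks the association.
4. Keep SHAP and other XAI output as description, and interpret rankings only for models that beat the circular-shift reference. Otherwise report that no feature was identified.

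The cost is a few sentences and modest extra computing, with no new data. The downside is that some patients will have no relevant feature reported. The simulations show that held-out scoring separates no association from strong effects. They did not test its sensitivity at r = 0.2, so the gain there is protection against naming the wrong feature, not assured detection.
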